# Rationale and design of an investigator-initiated, multicenter, prospective open-label, randomized trial to evaluate the effect of ipragliflozin on endothelial dysfunction in type 2 diabetes and chronic kidney disease: the PROCEED trial

**DOI:** 10.1186/s12933-020-01065-w

**Published:** 2020-06-13

**Keywords:** Chronic kidney disease (CKD), Endothelial dysfunction, Ipragliflozin, Reactive hyperemia peripheral arterial tonometry (RH-PAT), Sodium glucose cotransporter 2 inhibitor (SGLT2i), Type 2 diabetes (T2D)

## Abstract

**Background:**

Type 2 diabetes (T2D) is associated with renal impairment and vascular endothelial dysfunction. Therefore, this pathological connection is an important therapeutic target. Recent cardiovascular and renal outcome trials demonstrated that sodium glucose cotransporter 2 inhibitors (SGLT2is) consistently reduced the risks of cardiovascular and renal events and mortality in patients with T2D and various other background risks including chronic kidney disease (CKD). However, the precise mechanisms by which SGLT2is accords these therapeutic benefits remain uncertain. It is also unknown whether these SGLT2is-associated benefits are associated with the amelioration of endothelial dysfunction in patients with T2D and CKD.

**Methods:**

The PROCEED trial is an investigator-initiated, prospective, multicenter, open-label, randomized-controlled trial. The target sample size is 110 subjects. After they furnish informed consent and their endothelial dysfunction is confirmed from their decreased reactive hyperemia indices (RHI), eligible participants with T2D (HbA1c, 6.0–9.0%) and established CKD (30 mL/min/1.73 m^2^ ≤ estimated glomerular filtration ratio [eGFR] < 60 and/or ≥ urine albumin-to-creatinine ratio 30 mg/g Cr) will be randomized (1:1) to receive either 50 mg ipragliflozin daily or continuation of background treatment (non-SGLT2i). The primary endpoint is the change in RHI from baseline after 24 weeks. To compare the treatment effects between groups, the baseline-adjusted means and their 95% confidence intervals will be estimated by analysis of covariance adjusted for HbA1c (< 7.0% or ≥ 7.0%), age (< 70 y or ≥ 70 y), RHI (< 1.67 or ≥ 1.67), eGFR (< 45 mL/min/1.73 m^2^ or ≥ 45 mL/min/1.73 m^2^), and smoking status. Prespecified responder analyses will be also conducted to determine the proportions of patients with clinically meaningful changes in RHI at 24 weeks.

**Discussion:**

PROCEED is the first trial to examine the effects of ipragliflozin on endothelial dysfunction in patients with T2D and CKD. This ongoing trial will establish whether endothelial dysfunction is a therapeutic target of SGLT2is in this population. It will also provide deep insights into the potential mechanisms by which SGLT2is reduced the risks of cardiovascular and renal events in recent outcome trials.

*Trial registration* Unique Trial Number, jRCTs071190054 (https://jrct.niph.go.jp/en-latest-detail/jRCTs071190054).

## Background

Type 2 diabetes mellitus (T2D) is often associated with microvascular complications, such as impaired kidney function, and is a major cause of chronic kidney disease (CKD) and end-stage renal disease (ESRD) [1, 2]. CKD is one of the strongest established risk factors for cardiovascular events and increased mortality [3, 4]. Over the past two decades, intensive blood glucose control and interventions targeting multiple risk factors have been recognized as established therapeutic strategies to reduce the risk of microvascular complications and improve outcome [5, 6]. Renin-angiotensin-aldosterone system (RAAS) blockade is the only medication approved for preventing decline in kidney function and development of ESRD in patients with T2D [7, 8]. Nevertheless, many people diagnosed with T2D still present with CKD and ESRD [9] and, by extension, an important residual risk of worsened health outcomes. Therefore, the development of effective supplementary renoprotective therapies for patients with T2D is urgently required.

A sodium glucose co-transporter 2 inhibitor (SGLT2i) was formulated to reduce blood glucose by blocking glucose reabsorption at the renal proximal tubule. Recent cardiovascular outcome trials (CVOT) demonstrated that SGLT2is improved cardiorenal outcomes in a wide range of patients with T2D [10, 11]. SGLT2is also consistently prevented decline in renal function and reduced CKD progression in the aforementioned CVOTs [12–14]. The CREDENCE trial showed that canagliflozin markedly reduced the risks of composite renal events and mortality in patients with T2D and established CKD [15]. A systematic review and meta-analysis of pooled data from four CVOTs revealed that SGLT2is reduced the risk of composite renal events across all studies irrespective of the baseline levels of renal function, such as estimated glomerular filtration ratio (eGFR) and albuminuria, and baseline RAAS blockade use [16]. The available evidence indicates that these renal effects may be a class effect of SGLT2is [17, 18]. Hence, SGLT2is have become the guideline-recommended treatment option for patients with T2D who are at high risk of cardiovascular events and renal insufficiency [19, 20].

To date, various mechanisms have been proposed to explain the renoprotective efficacy of SGLT2is. One plausible theory is that they modulate renal hemodynamics by correcting intraglomerular hyperfiltration [21–24], independent of their glucose-lowering effect [25]. However, the underlying mechanisms responsible for the cardiorenal outcomes of SGLT2i therapy and the influences of these agents on other drivers remain to be elucidated. Thus, we are currently focusing on the effects of SGLT2is on endothelial function in patients with T2D and CKD. Endothelial function may be impaired by various metabolic disturbances, such as insulin resistance and diabetes [26]. Elevated markers indicative of endothelial dysfunction are associated with T2D [27–29]. Endothelial dysfunction is also associated with renal impairment and CKD pathogenesis [30, 31]. Therefore, endothelial dysfunction plays pivotal roles in the development of the pathogenic triangle of T2D and CKD (Fig. 1). The PROCEED trial was designed to test the hypothesis that SGLT2is can break this triangle. Here, we will assess the therapeutic efficacy of SGLT2is on endothelial dysfunction in the attempt to clarify the mechanisms by which SGLT2is confers cardiovascular and renal benefits in patients with T2D and CKD.

**Fig. 1 Fig1:**
[figure not shown]
Rationale for the PROCEED trial. Endothelial dysfunction is closely associated with T2D and CKD and forms a pathological triangle. The objective of our trial is to test the hypothesis that SGLT2-mediated inhibition breaks this triangle by ameliorating endothelial dysfunction. Another aim is to elucidate the mechanisms by which SGLT2 inhibitors confer cardiovascular and renal benefits in patients with T2D and CKD. *CKD*: chronic kidney disease; *SGLT2*: sodium-glucose cotransporter 2; *T2D*: type 2 diabetes

## Methods

### Trial overview and design

The Program of Ipragliflozin for Endothelial Dysfunction in Chronic Kidney Disease and Type 2 Diabetes (PROCEED) trial is an ongoing, investigator-initiated, prospective, multicenter, open-label, randomized-controlled trial. Informed consent will be received from eligible subjects and they will be randomized into ipragliflozin or non-SGLT2is use (control) groups. Each treatment regimen will be followed for 24 mo. The effects of ipragliflozin on endothelial dysfunction in comparison to the control will be evaluated by RH-PAT.

Local certified review boards (CRB) approved the trial protocol (No. C20190201). The trial must be conducted in full compliance with the articles of the Declaration of Helsinki and in accordance with the Clinical Trial Act in Japan. The PROCEED trial was entered into the Japan Registry of Clinical Trials (ID: jRCTs071190054) and is funded by Astellas Pharma Inc. However, this funding agency has no role in trial design or execution.

### Trial population and recruitment

A total of 110 participants will be recruited across six sites in Japan. Trial recruitment began in March 2020 and is expected to end by August 2021. Eligible participants are patients aged ≥ 30 y who meet the inclusion and exclusion criteria detailed in Table 1. Eligible patients include those with a diagnosis of T2D, a HbA1c in the range of 6.0–9.0%, on stable glucose-lowering agents for ≥ 3 mo before providing consent, and presenting with established CKD (30 mL/min/1.73 m^2^ ≤ eGFR < 60 and/or ≥ urine albumin-to-creatinine ratio (UACR) 30 mg/g Cr). However, they must have no history of clinically apparent atherosclerotic cardiovascular diseases such as coronary artery disease, stroke, peripheral artery disease, and symptomatic carotid artery stenosis. Based on the recently proposed value for the RH-PAT-derived reactive hyperemia index (RHI) distinguishing normal and impaired endothelial function, RHI ≥ 2.10 is a plausible marker of normal endothelial function [32]. Subjects with RHI < 2.10 at the time of pre-testing RH-PAT ≤ 3 mo prior to randomization were eligible for the present trial. In this way, subjects with normal endothelial function were excluded. After initial eligibility screening using prior medical records, each patient will receive an adequate explanation of the trial plan before they are asked to provide written informed consent.

**Table 1 Tab1:** Comprehensive inclusion and exclusion criteria

Inclusion	Exclusion
Adults (aged ≥ 30 years) T2D with HbA1c ≥ 6.0% and < 9.0% Pre-existing CKD with (i) 30 mL/min/1.73 m^2^ ≤ eGFR < 60 mL/min/1.73 m^2^ and/or (ii) albuminuria ≥ 30 mg/g Cr Patients with RHI < 2.10 at pre-testing RH-PAT within 3 mo prior to randomization Patients who received an explanation of the study and provided written informed consent	Type 1 diabetes History of clinically apparent atherosclerotic CVDs such as CAD, stroke, PAD, and symptomatic carotid artery stenosis History of arterial fibrillation History of severe ketosis, diabetic coma, or precoma attack ≤ 6 mo prior to informed consent Severe renal dysfunction (eGFR < 30 mL/min/1.73 m^2^ or undergoing dialysis) Patients received SGLT2is within 3 mo before informed consent Patients who changed the glucose-lowering medications within 3 mo before informed consent Hypersensitivity to ipragliflozin or other SGLT2is Symptomatic hypotension, or systolic blood pressure < 90 mm Hg Patients with severe infection or trauma at screening Patients in perioperative period around screening Polysystic kidney disease, lupus nephritis, or ANCA-related vasculitis Pregnant or suspected pregnancy Considered inappropriate for the study by investigators due to other reasons such as malignancy

*ANCA* antineutrophil cytoplasmic antibody; *CAD* coronary artery disease; *CVDs* cardiovascular diseases; *CKD* chronic kidney disease; *eGFR* estimated glomerular filtration rate; *PAD* peripheral artery disease; *RHI* reactive hyperemia index; *RH*-*PAT* reactive hyperemia peripheral arterial tonometry; *SGLT2is* sodium glucose cotransporter 2 inhibitors; *TIA* transient ischemic attack; *T2D* type 2 diabetes

### Trial design and follow-up

All consenting and eligible participants will be randomized and assigned either to the ipragliflozin group or the non-SGLTis use (control) group. There will be a follow-up visit to measure the study endpoints either at 24 weeks or at discontinuation (Fig. 2). However, all participants will visit their regular physicians at unprescribed time points in order to receive usual care, individualized background treatment, administration of the study drug, and monitoring of safety information and drug adherence during the study period.

**Fig. 2 Fig2:**
[figure not shown]
Trial design. *SGLT2is*: sodium-glucose cotransporter 2 inhibitors; *T2D*: type 2 diabetes

### Randomization

All participants who signed informed consent and met the enrollment criteria will be randomly assigned (1:1) either to the ipragliflozin treatment or the non-SGLT2is (control) group (Fig. 2). Treatments will be assigned via a web-based program, the minimization method, and biased coin assignment balancing by age (< 70 y; ≥ 70 y), HbA1c level (< 7%; ≥ 7%), current smoking (yes, no), pre-testing RHI (< 1.67; ≥ 1.67), and eGFR (< 45 mL/min/1.73 m^2^; ≥ 45 mL/min/1.73 m^2^) at the time of screening.

### Treatment

All participants will be followed for 24 months. No specific numerical glycemic control target such as the HbA1c level was set for this study. Nevertheless, all participants must be treated in order to achieve a personalized goal recommended by the Japanese treatment guideline [33, 34]. Participants assigned to the ipragliflozin group will receive 50 mg ipragliflozin once daily in addition to their background therapy. If the personalized goal is not achieved, the ipragliflozin dose may be increased by the investigators to 100 mg once daily. Participants assigned to the control group will continue their background therapy. Within the appropriate range of the therapeutic goal, participant background therapy will not change during the study. However, if participants cannot reach their glycemic target, co-administration of antidiabetic agents other than SGLT2 inhibitors or increased dosages of other antidiabetic agents may be considered by the investigators. If the blood glucose level is > 13.3 mmol/L (> 240 mg/dL) after an overnight fast and is confirmed by a second measurement on a different day, rescue medication may be initiated for hyperglycemia treatment. The initiation, choice, and dosage of the rescue medication(s) are left to the discretion of the investigator. Rescue medication may include an up-titration of a background treatment. If insulin is a background therapy, a change of > 10% of the total daily prescribed insulin dose is considered rescue therapy. All rescue medication must be taken in accordance with the prescribing information in order to minimize the risks of contraindications and hypoglycemia. Upon trial completion, participants may select any glucose-lowering treatment in accordance with their individual requirements.

### Measurements

The baseline characteristics of all participants including gender, age, body height, body weight (BW), abdominal circumference, office blood pressure (BP), pulse rate (PR), duration of T2DM, complications, background treatment, and smoking habit will be recorded prior to randomization. The background treatment and trial medication and adherence will be recorded for each patient at each visit. Abdominal circumference, BW, BP, and PR will be measured at baseline and at 24 weeks. The following assessments and methodology will be also applied at baseline and at 24 weeks: peripheral endothelial function according to the RH-PAT test, echocardiography (left ventricular ejection fraction determined by a modified Simpson method, left atrial volume index, E, septal e’, lateral e’, and E/e’ by tissue Doppler imaging), and non-contrast abdominothoracic computed tomography (CT) to measure pericardiac, hepatic, and perirenal fatty tissue, renal size, and blood and urine samples. (Please see Additional file 1). Certain serum biomarkers including *N*-terminal pro-brain natriuretic peptide, erythropoietin, cystatin C, and procollagen III peptide will also be measured at the central laboratory of SRL Inc., Tokyo, Japan. Images of non-contrast abdominothoracic CT will be measured at the core laboratory of the Department of Diabetes, Endocrinology, and Metabolism, Fukushima Medical University, Fukushima, Japan.

### Measurement of RH-PAT

Peripheral endothelial function will be evaluated by RH-PAT using an Endo-PAT2000 device (Itamar Medical, Caesarea, Israel). RH-PAT principles and procedures have been described elsewhere [35–37]. In brief, the measurements will be performed in the mornings at baseline and at 24 wks in a quiet, light- and temperature-controlled room. The patients will be fasted and in stable condition before taking their daily medication. A BP cuff will be placed on the upper arm of the patient and the opposite arm will serve as a control. The PAT probes will be placed on one finger of each hand. The patient will be allowed to rest for ≥ 15-min on a bed in a supine position and his or her baseline pulse amplitude will be recorded from each fingertip for 6 min. The BP cuff will be inflated to 60 mmHg above systolic BP or to 200 mmHg for 5 min. The cuff will then be deflated and the pulse amplitude will be recorded for 5 min. The RHI will be automatically calculated in an operator-independent manner by a computerized algorithm. The augmentation index (AI), heart rate variability (HRV), standard deviation of the normal to normal intervals (SDNN), and the ratio of low-to high-frequency (LF/HF) will be automatically calculated using Endo-PAT2000 software (v. 3.4.4; Itamar Medical, Caesarea, Israel).

### Trial endpoints

The primary endpoint in this trial is the change in natural log-transformed RHI (LnRHI) from baseline to 24 weeks or discontinuation. The secondary endpoints include (i) the  % change in LnRHI from baseline to 24 weeks or discontinuation, (ii) the proportion of patients with clinically meaningful changes in LnRHI (≥ 15% increase from baseline at 24 weeks or discontinuation), (iii) the proportion of patients with clinically meaningful improvement in RHI (≥ 2.10 at 24 weeks or discontinuation), (iv) the proportion of patients attaining (ii) and/or (iii), and (v) the proportion of patients with clinically meaningful changes in LnRHI (≥ 15% decrease from baseline at 24 weeks or discontinuation). Additional efficacy endpoints include changes from baseline to 24 weeks or discontinuation in (i) blood and urine laboratory values (Additional file 1), (ii) vital signs including abdominal circumference, BP, PR, BW, and body mass index, (iii) vascular functional parameters (AI, HRV, SDNN, and LF/HF) measured by a RH-PAT device, (iv) left ventricular systolic and diastolic function measured by echocardiography, and (v) pericardiac, hepatic, and perirenal fatty tissue and renal size measured by non-contrast abdominothoracic CT.

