#### Statistical analysis plan

Summary statistics will be used to calculate all baseline characteristics including the categorical variable frequencies and proportions and the normally distributed mean ± standard deviation or median [interquartile range] with skewed distribution for the continuous variables. Patient characteristics will be compared by Fisher’s exact test for categorical variables and the Wilcoxon rank sum test for continuous variables.

Analyses of the primary and secondary endpoints will be performed for the full analysis set (FAS). The FAS excludes all participants with no post-randomization efficacy endpoint data and those deemed ineligible after registration because they failed to provide informed consent or did not meeting the study eligibility criteria.

The primary endpoint was a comparison of treatment effects between treatment groups. The baseline-adjusted least-square means (LSM) and their 95% confidence intervals (CI) will be estimated by analysis of covariance (ANCOVA) for the FAS. For a secondary analysis of the primary endpoint, an analysis of variance including allocation factors and treatment group as factors will also be performed. As a supplementary analysis, the primary endpoint will also be analyzed in the per protocol set excluding subjects seriously violating the trial protocol. Prespecified subgroups stratified according to clinical characteristics based on, but not limited to, the RHI at baseline (< 1.67 or ≥ 1.67) will be analyzed for the primary endpoint as described above.

For the secondary endpoints, (i) the % change in LnRHI from baseline to 24 wks or discontinuation will be analyzed by a two-sample *t* test. Their LSMs and 95% CIs will be calculated and the treatment effects will be compared between groups. (ii) The proportions of patients presenting with clinically meaningful changes in LnRHI or RHI will be analyzed with a logistic regression model adjusted by the corresponding baseline values to calculate the odds ratios and their 95% CIs and compare the treatment effects between groups.

Changes in the additional efficacy endpoints from baseline to 24 weeks or discontinuation will be analyzed by ANCOVA as for the primary endpoint. The LSMs and their 95% CIs will be calculated and the treatment effects will be compared between groups. Pearson’s correlation coefficients will be used to identify the correlations between the changes in RHI from baseline and each of the additional efficacy endpoints.

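### Secondary endpoint (i) is a percentage of LnRHI, a log value that can be near zero or negative, so it is unstable; the 15% rule in (ii), (iv) and (v) sets a bar that depends on baseline

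*Protocol article*

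**What the plan says.** In the protocol article, Trial endpoints, the primary endpoint is an absolute change on the log scale: "The primary endpoint in this trial is the change in natural log-transformed RHI (LnRHI) from baseline to 24 weeks or discontinuation". Secondary endpoint (i) is the % "change in LnRHI from baseline to 24 weeks or discontinuation, (ii) the proportion of patients with clinically meaningful changes in LnRHI". The responder rule in (ii) is "clinically meaningful changes in LnRHI (≥ 15% increase from baseline at 24 weeks or discontinuation", and the worsening rule in (v) is "clinically meaningful changes in LnRHI (≥ 15% decrease from baseline at 24 weeks or discontinuation". Endpoint (iv) combines (ii) with (iii), and (iii) is an absolute cut on RHI: "the proportion of patients with clinically meaningful improvement in RHI (≥ 2.10 at 24 weeks or discontinuation".

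Under Statistical analysis plan, for (i), the % "change in LnRHI from baseline to 24 wks or discontinuation will be analyzed by a two-sample" t test. The responder endpoints go to a logistic regression adjusted for the corresponding baseline value.

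Table 1 requires a pre-test RHI below 2.10 and sets no lower limit. Nothing states how a baseline LnRHI at or below zero would be handled.

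**The concern.** A percentage change needs a baseline with a natural zero, well away from that zero. RHI has one; its logarithm does not. LnRHI is 0 when RHI is 1, so dividing by it gives very large values just above RHI 1 and the wrong sign below it. LnRHI is also already a relative scale: a fixed difference in LnRHI is the same percentage change in RHI at every baseline. Taking a percentage of it undoes that property.

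Two things are at stake. In (i), a few patients with low baselines can dominate the variance and hide a real difference. In (ii), (iv) and (v), one label for a meaningful change covers different changes in RHI, easiest to reach just above RHI 1. The article's Discussion names the responder analyses as a way to examine whether response differs by baseline level; a cut-off that itself moves with baseline builds part of that dependence in.

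**Working it through.** **Inputs from the protocol article.** Difference in LnRHI change 0.10, SD of change 0.15, two-sided 5%, 90% power, 98 patients (Sample size estimation); allocation 1:1 (Randomization); RHI below 2.10 at pre-test (Table 1). Arm changes of 0.05 and 0.15 are the planning values that the article reports for the cited dapagliflozin study; their difference is the 0.10 used here.

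**1. The plan's own figure.** The exact two-sample t test with difference 0.10 and SD 0.15 gives 90.4% power at 49 per arm (89.8% at 48), so 98 in total. The stated figure reproduces. It concerns the absolute change in LnRHI, not a percentage of it.

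**2. What the percentages mean.** Write b = ln(baseline RHI) and d = change in LnRHI. Endpoint (i) is 100 × d / b. A gain of d = 0.10 is always a rise in RHI of exp(0.10) - 1 = 10.5%. For b above 0, the rule in (ii) is d ≥ 0.15 b, that is, a rise in RHI of baseline^0.15 - 1.

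| Baseline RHI | b | (i) for d = 0.10 | RHI rise needed for (ii) |
|---|---|---|---|
| 2.09 | 0.737 | 13.6% | 11.7% |
| 1.90 | 0.642 | 15.6% | 10.1% |
| 1.67 | 0.513 | 19.5% | 8.0% |
| 1.30 | 0.262 | 38.1% | 4.0% |
| 1.10 | 0.095 | 105% | 1.4% |
| 1.02 | 0.020 | 505% | 0.3% |
| 0.90 | -0.105 | -95% | sign reversed |

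The planned gain of 0.10 meets (ii) only if b ≤ 0.10 / 0.15 = 0.667, that is, if baseline RHI is at most about 1.95. Just below the entry limit it fails.

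**3. Sign reversal.** RHI 0.95 to 1.05 gives (0.0488 + 0.0513) / (-0.0513) = -195%: an improvement that (v) counts as a worsening. RHI 0.90 to 0.80 gives +112%: a worsening that (ii) counts as a response.

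**4. Responders when the mean change is zero.** With SD 0.15 the chance of meeting (ii) is 1 - Φ(0.15 b / 0.15) = 1 - Φ(b): 23% at RHI 2.09, 30% at 1.67, 46% at 1.10. A fixed cut at ln 1.15 = 0.140 gives 1 - Φ(0.140 / 0.15) = 18% at every baseline.

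**5. Power for (i), by simulation.** Assumed, because the documents give no baseline distribution: true LnRHI normal with mean 0.50 to 0.55 and SD 0.10 to 0.20; within-person SD 0.15 / √2 = 0.106; pre-test below ln 2.10; 49 per arm; changes 0.05 and 0.15. Observed baseline SD is then about 0.14 to 0.20.
- t test on % change in LnRHI: about 20 to 71% power.
- t test on change in LnRHI: about 90%.
- Wider assumptions (baseline mean 0.40 to 0.55, SD 0.15 to 0.25, change independent of baseline): 13 to 84% against about 90%.
- Share of patients with baseline LnRHI below 0: about 0.01 to 1.5% in the first setting, up to 6% in the wider one.

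**6. Power for (ii) and (v) in the first setting, with the planned baseline-adjusted logistic regression.**
- (ii) as written: 66 to 80%. With a cut of 0.140 in LnRHI change: 76 to 83%.
- (v) as written: 36 to 49%. With a cut of ln 0.85 = -0.163: about 3 to 5%. Expected rates at that cut are Φ((-0.163 - 0.05) / 0.15) = 7.8% of controls and Φ((-0.163 - 0.15) / 0.15) = 1.9% on ipragliflozin, or about 4 and 1 of 49 patients.

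**The case against.** The strongest reply is that only secondary endpoints are touched, that none is protected for multiplicity, and that a detailed analysis plan is still to be confirmed before database lock. All of this is true and limits the severity. It does not remove the point, because these are stated endpoint definitions that an analysis plan would inherit.

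A reader might infer that the responder endpoints mostly count measurement noise. The documents do not support that. The SD of 0.15 is the planned SD of change and is not described as measurement error. The responder model is adjusted for baseline, and under that model (ii) as written performs nearly as well as a fixed cut except at the widest baseline spread. The higher rates in step 4 mainly show a lower bar. What stands is that the bar moves with baseline; adjusting for baseline does not change how a patient was labelled.

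A reader might also take the wrong-sign cases as common. Under the first set of assumptions they amount to between none and about 1.5 of 98 patients.

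The power loss for (i) is partly the choice of test: a rank test on the same percentages had 77 to 81% power in comparable runs. That tames the outliers but not the reversed signs.

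Three further inferences do not hold.
- The abstract's wording, "proportions of patients with clinically meaningful changes in RHI at 24 weeks", is not a separate contradiction about responders: the abstract condenses the primary endpoint to RHI in the same way.
- Promising least-squares means beside a t test is harmless, since with one factor they are the group means.
- The rule does not differ from a 15% RHI rise at every conceivable value: the two coincide at RHI 2.54. That is above the pre-test limit, though the limit does not formally bind the separate baseline reading.

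**Conclusion.** The point holds and should be fixed, but it does not threaten the trial's main result. Endpoint (i) is badly scaled by its own definition, and that follows from algebra alone. How much power it loses depends on an assumed baseline distribution: about 20 to 71% under the central assumptions and 13 to 84% over the wider range, against about 90% for the change in LnRHI. The baseline-dependent bar in (ii), (iv) and (v) needs no such assumption: the required rise in RHI runs from about 12% just under the entry limit to 1.4% at RHI 1.10. Counting an improvement as a worsening is possible but rare. The primary endpoint, its sample size of 98 and endpoint (iii) are sound on this point.

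**What to change.** Define (i) as the % change in RHI, 100 × (exp(change in LnRHI) - 1). Estimate it by back-transforming the baseline-adjusted ANCOVA difference and its confidence interval, in place of the t test on % LnRHI.

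Define (ii) and (v) by a fixed change in LnRHI, the same at every baseline, and set it before database lock. If a 15% change in RHI is what is meant, the cuts are +0.140 and -0.163. The documents do not say that it is, so the investigators must choose and justify the cut. Endpoint (iv) follows from (ii).

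No new data are needed, but there are costs:
- Endpoint (i) becomes a restatement of the primary result on the RHI scale.
- Responder proportions fall in both arms.
- At the 15%-of-RHI cut, (ii) keeps similar power (about 76 to 83%). Endpoint (v) becomes rare, about 8% of controls, with power of about 3 to 5% against 36 to 49% as written, and should be reported descriptively.
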